#### External beam equipment and techniques

Radiation therapy techniques that can be employed include three-dimensional conformal radiotherapy, forward intensity-modulated radiotherapy, inward intensity-modulated radiotherapy, volumetric modulated arc therapy and helical tomotherapy. Conventional radiotherapy (using a simulator for positioning and a two-dimensional planning system to design treatment plans with external and tangential fields) and proton therapy techniques are not allowed. Some variations in treatment planning and implementation are permitted to accommodate the participating centres in adapting to the research protocol. However, it is strongly recommended that the treatment plans for enrolled patients at each centre remain consistent to avoid confusion.

#### Dose prescription and fractionation

The whole breast target volume, or the integrated target volume of the whole breast and low to moderate axillary region, or the chest wall target volume, and the regional lymph node target volume receive a radiation dose of 5000 cGy in 25 fractions, delivered at a rate of 200 cGy per day, 5 days per week. Alternatively, a hypofractionated radiotherapy scheme can be chosen, with a radiation dose of 4000–4256 cGy in 15–16 fractions. For breast-conserving patients, a sequential tumour bed boost is performed after completion of WBI, as determined by individual centre investigators. It can be delivered using conventional fractionation, with a dose of 1000 cGy in 5 fractions at a rate of 200 cGy per day, or by using hypofractionation, with a dose of 798–1064 cGy in 3–4 fractions at a rate of 266 cGy per day. If there are high-risk factors for local recurrence, such as positive surgical margins, close margins or young age, the radiation dose for the tumour bed boost may be increased to 1400–1600 cGy in 7–8 fractions at a rate of 200 cGy per day (see online supplemental file 10 for details).

#### Dose and Volume Histogram (DVH) constraints

It is required that at least 95% of the prescribed dose to the PTV covers 95% of the PTV. The specific dose distribution is determined by each centre’s policy, with a recommended level as shown in online supplemental file 11. For breast-conserving patients, it is recommended achieving a central axis dose uniformity of ≤±7% for PTV_2 (whole breast or integrated target volume of whole breast and low to moderate axillary region) and PTV_1 (tumour bed), and minimising the volume receiving ≥105% of the prescribed dose. The constraints for OARs should follow the Quantitative Analysis of Normal Tissue Effects in Clinical guidelines (see online supplemental file 12).

### Withdrawal from research and study termination

#### Termination of treatment

Research treatment will be terminated if any of the following conditions occur in the patient:

The subject withdraws informed consent.Any adverse event (AE) causes the subject to be unable to continue participating in the study.The subject is lost to follow-up.The subject does not comply with the study requirements and/or the investigator’s instructions.The subject has a concomitant illness or change in the subject’s condition, and the investigator believes the subject is no longer suitable for the study treatment.For any other reason the investigator believes the subject is not suitable for continuing in the study.

If a subject drops out or withdraws, relevant safety and efficacy evaluations should be completed as soon as possible.

#### Study termination

The trial will be terminated if any of the following situations occur during the trial:

Serious safety issues arise during the trial.There is a major error in the study protocol.The principal investigator voluntarily stops the trial.The administrative authority revokes the trial.The termination of the trial may be temporary or permanent.

If the trial is terminated, all trial records should be retained for review.

#### Follow-up evaluation and toxicity assessment

The registration timeline, intervention measures and assessments are presented in online supplemental file 13. In the follow-up phase after radiotherapy, check-ups and assessments will be performed every 6 months until the occurrence of an endpoint event or the end of the study. For patients without postoperative radiotherapy, check-ups and assessments will be conducted every 6 months after the completion of adjuvant chemotherapy until the occurrence of an endpoint event or the end of the study. Effectiveness evaluations include tumour imaging examinations and assessments, brain MRI or CT, bone scans, quality of life questionnaires (EORTC QLQ-C30) and breast cancer-specific quality of life scales (EORTC QLQ-BS23). Safety evaluations include but are not limited to physical examinations, Eastern Cooperative Oncology Group Performance Status (ECOG PS) scores, pregnancy test checks, blood routine tests, blood biochemistry tests, AEs and serious AEs (SAEs). At the end of the study, participants will undergo physical examinations, performance status assessments (ECOG PS), blood routine tests, blood biochemistry tests, tumour markers, breast ultrasound/MRI, mammography, chest X-ray/CT, abdominal ultrasound/CT, and EORTC QLQ-C30 and EORTC QLQ-BS23 scoring. Evaluations of concomitant medications and AEs are also required. The end-of-study visit window is 60 months after the last participant completes radiotherapy. For participants who are withdrawn or drop out before the end of the study, safety and effectiveness assessments will be conducted according to the requirements of end-of-study safety and effectiveness visits.

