### Objectives and endpoints

This study aims to evaluate whether adjuvant radiotherapy to the regional lymph nodes after BCS or chest wall plus regional lymph node radiotherapy after total mastectomy can further improve clinical outcomes in N1 patients with low clinical risk but high RecurIndex-LRR risk.

The primary endpoint is invasive disease-free survival (IDFS). Secondary endpoints are AFR, LRR-free survival (LRFS), DMFS, RFS, OS, DFS, BCSM and patient quality of life assessment. The specific definitions can be found in table 1.

**Table 1 T1:** The specific definitions of the study endpoints

IDFS	The time from the day the subject is randomised to the earliest occurrence of invasive cancer local recurrence, distant metastasis or death, but does not include contralateral breast second primary cancer.
AFR	Any ipsilateral chest wall, breast, regional lymph node recurrence or distant metastasis event that occurs during the follow-up period.
LRFS	The time from the day the subject is randomised to the earliest occurrence of ipsilateral chest wall, breast, or regional lymph node recurrence or death.
DMFS	The time from the day the subject is randomised to the earliest occurrence of distant metastasis or death.
RFS	The time from the day the subject is randomised to the earliest occurrence of ipsilateral chest wall, breast, regional lymph node recurrence, distant metastasis or death.
OS	The time from the day the subject is randomised until the patient’s death.
DFS	The time from the day the subject is randomised to the recurrence of the disease or the patient’s death due to disease progression.
BCSM	The time from the day the subject is randomised to death from breast cancer.

AFRany first recurrenceBCSMbreast cancer-specific mortalityDFSdisease-free survivalDMFSdistant metastasis-free survivalIDFSinvasive disease-free survivalLRFSlocal–regional recurrence-free survivalOSoverall survivalRFSrecurrence-free survival

During the screening period and 3 months after the end of treatment, patients in each group fill out the quality of life questionnaire (EORTC Core Quality of Life Questionnaire (EORTC QLQ-C30)), as well as the breast cancer survival quality scale (EORTC Breast Cancer-Specific Quality of Life Questionnaire (EORTC QLQ-BS23)) annually during the follow-up phase (onlinesupplemental files 2  3).

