### Statistical analysis

Descriptive statistical analyses will be conducted based on demographic characteristics such as age, gender, height, weight and other baseline characteristics such as medical history. The Cox proportional hazards model will be used for analysis of the primary endpoint. The HR and its 95% CI will be calculated, including stratification factors and other covariates. Additionally, the Cox proportional hazards model without covariates will be used to support the analysis results of the primary endpoint. Moreover, the Kaplan-Meier (KM) method will be used to calculate the median IDFS for the two groups (experimental group vs control group), including 95% CIs. KM plots will be used to illustrate the time trends of IDFS. For the secondary endpoints, the AFR of each group will be calculated, as well as the corresponding 95% Clopper-Pearson CIs. LRFS, DMFS, RFS, OS, DFS and BCSM will be analysed for median values using the KM method (including 95% CIs). The overall changes in EORTC QLQ-C30 and EORTC QLQ-BS23 scores from baseline will be summarised. Safety analysis will be conducted by summarising AEs, changes in laboratory test results, changes in vital signs and study treatment exposure. The results will be reported by treatment group. All AEs during treatment, grade 3 or higher treatment-emergent AEs (TEAEs), SAEs, radiotherapy-related SAEs and TEAEs leading to study termination will be summarised by organ system, preferred term, and group in terms of numbers and percentages (see online supplemental file 16 for details). A p value of ≤0.05 in a two-tailed test will be considered statistically significant. Statistical analyses will be performed using SPSS V.25.0 and STATA V.14.

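### As worded, follow-up in both arms stops at an undefined endpoint event, which conflicts with the definitions of OS, BCSM, LRFS and, to a lesser degree, DMFS

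*Protocol article*

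**What the plan says.** The protocol article, under Follow-up evaluation and toxicity assessment, sets one visit rule in two sentences. Once irradiation has finished, "check-ups and assessments will be performed every 6 months until the occurrence of an endpoint event or the end of the study". Where a patient is not irradiated after surgery, the schedule is "every 6 months after the completion of adjuvant chemotherapy until the occurrence of an endpoint event or the end of the study". The first sentence covers the experimental arm and the breast-conserving controls, who receive whole breast irradiation. The second covers the mastectomy controls. The rule therefore applies in both arms. The article does not say which endpoint's event is meant.

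Table 1, under Objectives and endpoints, defines the outcomes:

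- IDFS runs to the "earliest occurrence of invasive cancer local recurrence, distant metastasis or death".
- LRFS runs to the "earliest occurrence of ipsilateral chest wall, breast, or regional lymph node recurrence or death". Distant metastasis is not an event.
- DMFS is "The time from the day the subject is randomised to the earliest occurrence of distant metastasis or death". Local-regional recurrence is not an event.
- OS runs from randomisation to death from any cause.
- BCSM is "The time from the day the subject is randomised to death from breast cancer".

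Under Statistical analysis, "LRFS, DMFS, RFS, OS, DFS and BCSM will be analysed for median values using the KM method".

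**The concern.** A local recurrence is an event for IDFS, AFR, LRFS and RFS. A distant metastasis is an event for IDFS, AFR, DMFS and RFS. Either one is an endpoint event in the ordinary sense and would end the scheduled visits. Yet four secondary endpoints need information from after that point: OS and BCSM need the later death, DMFS a metastasis that follows a local-regional recurrence, and LRFS a local-regional failure or death that follows a metastasis.

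Kaplan-Meier estimation assumes that censored patients have the same future risk as those still followed. A patient censored for OS at recurrence has a much higher risk of death than one who stays under observation, so the censoring is informative and the curves read too high. Under the planning assumptions more controls than experimental patients have a first event, so more controls would be lost before death and a true survival difference would look smaller. The article's Introduction and Discussion rest much of the case for nodal irradiation on survival and breast cancer mortality, and those are the endpoints most exposed.

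**Working it through.** **Planning inputs (Sample size estimation).** 5-year IDFS is 89% and 82%. Enrolment lasts 5 years, with 5 years of further follow-up. There are 216 patients per group before a 20% dropout allowance and 270 after it.

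The plan's own figures first: HR = ln 0.89 / ln 0.82 = 0.1165 / 0.1985 = 0.587, as stated; and 216 / 0.80 = 270, as stated.

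**Expected first IDFS events.** Take exponential IDFS and uniform accrual. With h = −ln S(5), the event probability over 5 to 10 years of follow-up is P = 1 − (e^(−h) − e^(−2h)) / h.

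- Experimental: 1 − (0.8900 − 0.7921) / 0.1165 = 0.160
- Control: 1 − (0.8200 − 0.6724) / 0.1985 = 0.256
- Mean 0.2081, giving 0.2081 × 432 = 89.9 events, or 0.2081 × 540 = 112.4

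Per 270 patients that is about 43 first events in the experimental arm and 69 in the control arm.

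**What the literal rule leaves.** If observation stops at the first IDFS event, an endpoint sees only first events of its own types. If a share q of first events is of those types, the stopped Kaplan-Meier value at 5 years is S(5)^q, and the recorded count is 270 × P × q. For example, if 15% of first events are deaths, control OS at 5 years reads 0.82^0.15 = 0.971, from 69.2 × 0.15 = 10.4 recorded deaths.

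**What full follow-up would show.** This needs quantities that the article does not give, so the following is an illustration by simulation. Assumptions:

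- First events split as local-regional/distant/death 30/55/15, 40/50/10 or 20/50/30 (%).
- Yearly hazards: distant metastasis after local-regional recurrence 0.15; death after distant metastasis 0.30; death after local-regional recurrence 0.02; local-regional recurrence after distant metastasis 0.10.
- Follow-up uniform on 5 to 10 years.

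Ranges over the three splits:

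| Endpoint | Events still recorded | Control 5-year estimate, full follow-up | Control, stopped at first event | Arm difference, full (points) | Arm difference, stopped (points) |
|---|---|---|---|---|---|
| OS | 19–45% | 89.7–92.6% | 94.3–98.0% | 3.0–4.0 | 0.9–2.3 |
| LRFS | 54–59% | 85.8–86.1% | 90.6–91.5% | 5.4–5.6 | 3.3–3.8 |
| DMFS | 77–90% | 84.5–86.7% | 85.4–88.7% | 5.3–5.9 | 4.6–5.7 |

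Recorded deaths per 270 fall from about 22–29 to 4–13 in the experimental arm and from about 36–46 to 7–21 in the control arm. BCSM was not simulated separately. It shares the mechanism of OS, because breast cancer deaths normally follow a recurrence.

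**The case against.** Four points can fairly be made for the plan.

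1. **The text does not say first event.** It could be read endpoint by endpoint, with OS and BCSM running to death. The term is undefined, so this is possible, but it is strained for a sentence that governs a single visit schedule. A centre could reasonably stop visits at recurrence.
2. **The rule stops visits, not survival data.** Nothing says that vital status ceases to be collected or that OS is censored at recurrence. The same section refers to supplemental file 13 for the schedule, and that file is not shown. It may contain survival follow-up. This point stands and limits how firmly the defect can be asserted.
3. **Other text suggests later contact.** The end-of-study examinations are not restricted to event-free participants, and the sample size section mentions efficacy follow-up to 10 and 15 years. Neither is said to cover patients after a recurrence, however, and the long-term follow-up appears only as a reason for the dropout allowance.
4. **Only secondary endpoints are involved.** For these the article plans Kaplan-Meier medians with confidence intervals and states no between-arm test. This stands and bears on severity.

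A reader might infer that the four endpoints cannot be estimated at all, or that BCSM events would fall almost to zero. The documents do not support that. It would need the strictest reading of the rule and no other route by which deaths reach the database. Even on the strict reading a curve can be drawn, and most DMFS events survive in the illustration.

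**Conclusion.** The point holds as a conflict of wording with consequences for secondary endpoints. Followed literally, the visit rule in both arms ends systematic observation before OS, BCSM, LRFS and DMFS are complete as Table 1 defines them, and nothing in the article repairs this. The resulting bias is informative censoring. It is largest for OS and BCSM, intermediate for LRFS and smallest for DMFS.

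The 90 to 112 first events follow from the plan's own assumptions with exponential survival. The percentages of events retained do not: they rest on assumed event splits and post-recurrence hazards and show only plausible size.

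IDFS, RFS and AFR depend on the first event, so they are unaffected, taking the recurrence that ends follow-up to be an IDFS event as well. The sample size does not change. The wording should be fixed, but the primary analysis is not at risk.

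**What to change.** Amend both follow-up sentences, for patients with and without radiotherapy. Suggested text:

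*After any non-fatal event, vital status, cause of death, first local-regional recurrence and first distant metastasis continue to be collected at least every 6 months until death, withdrawal of consent or end of study.*

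Also define endpoint event, and state that each secondary endpoint is ended or censored only according to its own definition: death for OS and BCSM (with cause of death for BCSM), distant metastasis or death for DMFS, and local-regional recurrence or death for LRFS. If supplemental file 13 already provides survival follow-up, bring the two texts into line.

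The cost is an amendment and brief status contacts for at most about 90 to 112 patients. It is best done now: enrolment is planned to about January 2028 and primary data collection to December 2032, so most events should lie ahead, and follow-up that is not recorded may not be recoverable later.

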## Materials and methods

The RIGAIN (RecurIndex-Guided postoperative radiotherapy with or without Avoidance of Irradiation of regional Nodes in 1–3 node-positive breast cancer) Study is a multicentre, prospective, randomised, open-label, phase III clinical trial that is being conducted in China. The overall research process is illustrated in figure 1. This study aims to screen postoperative patients with early-stage breast cancer (pT1–2N1M0) who have completed standard systemic therapy and possess eligible pathological specimens for participation. The inclusion and exclusion criteria are listed in box 1. RecurIndex testing will be performed using postoperative paraffin-embedded tissue sections from the primary lesion. The study is divided into a randomised controlled trial and an observational study based on clinical risk and RecurIndex-LRR risk. Patients with low clinical risk but high RecurIndex-LRR risk will be randomly assigned in a 1:1 ratio to either the experimental group (RNI) or the control group (no RNI), while patients with low clinical risk and low RecurIndex-LRR risk will be included in the observational study. This article primarily focuses on the randomised controlled trial. The study participants will receive the following treatments: experimental group: for patients who underwent BCS, RNI will be performed in combination with whole breast irradiation (WBI)+tumour bed boost irradiation. For patients who underwent mastectomy, chest wall irradiation (CWI) will be administered in combination with RNI. Control group: RNI will be omitted. For patients who underwent BCS, only WBI+tumour bed boost irradiation will be administered. For patients who underwent mastectomy, both RNI and CWI will be omitted. A comparative effectiveness analysis will be conducted. The study commenced in April 2023.

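### In the mastectomy stratum the 6-monthly visit clock depends on the randomised arm: negligible for the Cox HR, up to about one point at 5-year landmarks, and no defined quality-of-life anchor for controls

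*Protocol article*

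**What the plan says.** The section on follow-up evaluation and toxicity assessment sets two starting points for the same 6-monthly check-ups. Irradiated patients: "In the follow-up phase after radiotherapy, check-ups and assessments will be performed every 6 months". The others: "For patients without postoperative radiotherapy, check-ups and assessments will be conducted every 6 months after the completion of adjuvant chemotherapy". The evaluations listed there include imaging and both quality-of-life questionnaires.

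Materials and methods shows who falls under which rule.

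- **Mastectomy, experimental arm:** "For patients who underwent mastectomy, chest wall irradiation (CWI) will be administered in combination with RNI".
- **Mastectomy, control arm:** "For patients who underwent mastectomy, both RNI and CWI will be omitted".
- **Breast-conserving surgery (BCS), control arm:** "For patients who underwent BCS, only WBI+tumour bed boost irradiation will be administered". These patients are irradiated, like BCS patients in the experimental arm.

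Table 1 defines IDFS as "The time from the day the subject is randomised to the earliest occurrence of invasive cancer local recurrence", distant metastasis or death. The paragraph after Table 1 asks for quality-of-life forms "During the screening period and 3 months after the end of treatment", and annually during follow-up.

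**The concern.** Among randomised patients, only mastectomy controls are assigned no radiotherapy. BCS patients share one clock across arms; mastectomy patients do not. Screened patients have already completed systemic therapy, so the control clock starts before randomisation. The RNI clock starts after it. The endpoint is counted from randomisation in both.

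A recurrence found at a scheduled visit is dated by that visit. If the two arms are examined at different times since randomisation, part of any difference at a fixed time point is an artefact of the schedule, and a larger sample does not remove it. This matters for 5-year rates, on which the planning values of 89% and 82% are expressed. At the planned control rate about 67% (0.82 squared) would still be event-free at 10 years. The planned median IDFS is then unlikely to be reached, and readers will probably turn to the 5-year rate for the absolute benefit.

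For quality of life, an assessment tied to the end of treatment has no obvious date in patients who receive no study treatment.

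**Working it through.** **1. Offset between the grids.** Inputs: radiotherapy starts no later than 8 weeks after chemotherapy (Box 1), so the wait is 0-8 weeks. Radiotherapy takes 25 fractions at 5 per week (5 weeks) or 15-16 fractions (about 3 weeks) (dose prescription and fractionation).

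Offset d = wait + radiotherapy = (0 to 8) + (3 to 5) = 3 to 13 weeks, on a 26-week interval.

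**2. Planning values.** ln(0.89)/ln(0.82) = 0.587, which reproduces the stated HR. Yearly hazards: control -ln(0.82)/5 = 0.0397; experimental -ln(0.89)/5 = 0.0233.

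**3. Direction at a landmark.** Control visits fall at or shortly before each half-year from randomisation, and RNI visits fall 3-13 weeks after it. When a landmark lies between a control visit and the next RNI visit, the last RNI look is 26 - d weeks older. With no true effect, RNI is then too high by

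0.82 × (exp(0.0397 × (26 - d)/52) - 1).

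- d = 13 (gap 13 weeks): 0.8 points
- d = 9 (gap 17 weeks): 1.1 points
- d = 3 (gap 23 weeks): 1.5 points, with perfectly punctual visits

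For the remaining 26 - d weeks of each cycle the control look is older by d weeks, and the sign reverses: 0.82 × (exp(0.0397 × d/52) - 1) = 0.2 points (d = 3) to 0.8 points (d = 13) against RNI. Over a cycle the two phases roughly cancel.

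**4. Simulation.** 1,000,000 mastectomy patients per arm; exponential IDFS; all events found at visits; visits spread by ±2 weeks; follow-up of 5-10 years with an end-of-study visit. Weeks from chemotherapy end to randomisation, and from randomisation to radiotherapy end, were varied because the article does not give the split.

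| Weeks before / after randomisation | HR, planned effect | HR, no effect | 5-year difference, planned effect (points) | 5-year difference, no effect (points) |
|---|---|---|---|---|
| 0 / 3 | 0.582 | 0.989 | 7.13 | 0.70 |
| 4 / 5 | 0.583 | 0.993 | 7.62 | 1.15 |
| 4 / 9 | 0.585 | 0.996 | 7.46 | 0.90 |
| 8 / 5 | 0.585 | 0.996 | 7.37 | 0.90 |
| 0 / 13 | 0.585 | 0.995 | 6.73 | 0.08 |
| Common clock | 0.585 | 0.996 | 6.73 | 0.07 |

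The no-effect HR is 0.996 even with exact event times, so that departure from 1 is sampling noise. Against the common clock, the HR moves by at most 0.7% (0.989 against 0.996). The 5-year difference moves by 0 to +0.9 points under the planned effect (7.62 - 6.73) and by 0 to +1.1 under no effect (1.15 - 0.07). It is near zero in the 0 / 13 case because control visits then straddle the 5-year mark.

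**5. Size against the primary test.** The design implies about 111-116 events, so SE(log HR) is about 2/√111 = 0.19. The largest log-HR shift, ln(0.996/0.989), is about 0.007, or roughly 4% of one standard error if every patient had mastectomy.

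**6. Quality of life.** If the end of chemotherapy stands in for the end of treatment, the first form in mastectomy controls falls about 13 weeks after chemotherapy. In RNI mastectomy patients it falls 3 to 13 weeks later, at 16-26 weeks.

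**The case against.** The strongest reply is that this hardly touches what the trial will test. The primary analysis is a Cox HR, and the arms share the same interval and a common end-of-study visit. The statistical analysis section names HRs, medians and Kaplan-Meier plots, but no 5-year comparison. Deaths and symptomatic recurrences are not dated by visits, so the simulated shifts are upper bounds for the timings run. The mastectomy share is not given; at an assumed 50%, a 1.1-point shift becomes about 0.5 points overall. The detailed schedule is in supplemental file 13, which is not shown. All of this stands, and it limits the point.

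It does not remove the point. The article states the two clocks expressly, so this is a stated rule and not a missing detail.

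Three stronger inferences are tempting, and the documents do not support them.

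- **That the primary result is materially biased toward RNI.** The HR shift is too small for that.
- **That the RNI curve is too high throughout.** The offset alternates in sign: it favours RNI at whole-year landmarks and reverses between them.
- **That quality of life is biased in favour of irradiation.** The article does not define the end of treatment for mastectomy controls. The 13-week figure rests on one reading, and no direction has been shown.

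**Conclusion.** The point holds as a limited design flaw. Within the mastectomy stratum the assessment clock is set by the randomised arm, while IDFS runs from randomisation. The grids differ by about 3-13 weeks in 26.

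- **Primary HR:** a change of about 1% or less; no threat to the primary test.
- **5-year Kaplan-Meier difference:** 0 to about +1.1 points in favour of RNI in the timings simulated, in this stratum only. The formula reaches 1.5 points at the shortest offset with exactly punctual visits.
- **Quality of life:** the timing is undefined for mastectomy controls. On the chemotherapy reading it confounds time since chemotherapy with arm.

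These figures assume that randomisation falls between the end of chemotherapy and the start of radiotherapy, that hazards are constant at the planning values, and that all events are found at visits. The effect on the whole trial depends on the unknown mastectomy share.

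**What to change.** Schedule all efficacy and quality-of-life assessments from the date of randomisation, in both arms and after both types of surgery, with the same 6-month interval and the same visit windows. Replace the quality-of-life time point tied to the end of treatment by one fixed time from randomisation for everyone. Reconcile the follow-up section with supplemental file 13.

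The cost is a changed sentence, a visit-window table and the mapping of visits already booked to the nearest window. Radiotherapy toxicity can be recorded at these same visits; any toxicity check that keeps its own clock may not coincide with them. Enrolment is planned until January 2028 and primary data collection until December 2032, so an early change would cover most 5-year assessments.
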